### Safety Evaluation and Adverse Events

We will minimize the occurrence of adverse events in this clinical trial to ensure the safety of each participant. A comprehensive physical safety examination will be performed on all volunteers before and after treatment, including vital signs (heart rate, blood pressure, and respiration), routine blood and urine tests, biochemical function tests, electrocardiography, and liver and kidney function tests. Possible adverse reactions in this study include pain during acupuncture, fainting, and skin breakage or other injury caused by improper handling. If the patient experiences acupuncture fainting because of weakness or excessive stress, the acupuncture treatment will be stopped immediately, and the patient will be placed in a comfortable position and given warm water until they recover. In addition, if pain or systemic adverse reactions are caused by excessive current and voltage intensity, the electroacupuncture instrument will be turned off immediately. After confirming that the patient has no adverse reactions, the electroacupuncture instrument will be properly connected and used correctly according to the operational requirements. We will not only record the occurrence of any of the abovementioned adverse events in the case report book but will also actively deal with them.

### Data Collection and Management

All participants’ information will be recorded in the case report form in a true, complete, accurate, and timely manner, and data entry will be performed using the Clinical Monitor Data Manager (Microsoft Corp) after completion of at least 5 case report forms. We will use a data entry program that is prepared by computer software for the double entry of data, which keeps the participant’s personal information strictly confidential during the entry process. To prevent data leakage and loss, these data will be stored by our data researchers on servers with passwords and access restrictions and will not be shared with third parties outside of the data recorders and data administrators without the express permission of the research team leader. The quality control team will regularly review the accuracy and reliability of our data, and if there is no objection to these data, we will lock the data. No further changes will be allowed to the locked data file, and the database will be handed over to the statistical analysts for statistical analysis as required by the statistical plan. All of the above data collectors and managers will be involved in this clinical trial only after passing a standardized training and assessment, and more importantly, an agreement will be signed with the data collectors and managers to ensure that they will not disclose any personal information of the participants.

### Statistical Analysis

All data will be statistically analyzed by professional statisticians using SPSS software (version 25.0). If the data involved satisfy the characteristic properties of a normal distribution with uniform variance, we will use the mean and SD to describe them; conversely, if the data are not normally distributed, we will use the median and IQR to describe them. All statistical results will be considered statistically significant at *P*<.05.

Neuropsychological scale scores, iron metabolism–related indicators, and brain iron deposition are all measurement data. Normally distributed data with uniform variance among 3 groups will be analyzed using 1-way ANOVA, followed by multiple comparisons using the least significant difference test, whereas those with nonnormal distributions will be compared using the Kruskal-Wallis test followed by the Mann-Whitney *U* test with Bonferroni correction. Correlations between neuropsychological scale scores and serum iron metabolism indexes and brain iron deposition in patients with VCI will be assessed using Pearson correlation analysis.

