### Sample Size

Previous clinical studies on patients with VCI treated with acupuncture reported that the scores on the MoCA scale of acupuncture-treated and base-treated patients with VCI at 4 weeks were mean 26.13 (SD 5.33) and mean 22.66 (SD 5.38), respectively. We set the significance level at .05 and calculated the sample size as follows:

N = 2 [(*Z*_α/2_ + *Z*_β_) σ / δ]^2^

N is the sample size in each group, and σ and δ represent the larger SD and mean difference between the 2 groups with values of 5.38 and 3.47, respectively. When α=.05 and β=.1, checking the table shows that *Z*_α/2_=1.96 and *Z*_β_=1.282. Substituting the above data into the formula, a minimum of 64 patients in the randomized acupuncture group or control group will be required, considering a 20% shedding rate.

A review of relevant studies indicates that in magnetic resonance imaging–based studies of cognitive impairment, statistical significance can be achieved with 12 or more cases [23,24]. Because of limitations in the experimental conditions (high scanning cost of magnetic resonance imaging and the need for high levels of participant cooperation during scanning), we estimate that approximately one-third of the estimated sample of patients with VCI will be included as study participants, and finally, 42 patients with VCI and 21 healthy controls will be included.

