### Outcome Measurements

#### Overview

The 3 main areas of assessment will include neuropsychological tests, SWI, and serum iron metabolism. Researchers who are blinded to the treatment allocation will carry out all treatment evaluations.

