#### Serum Iron Metabolism–Related Indicators

A total of 4 mL of blood will be collected from patients in the morning on an empty stomach. The supernatant will then be extracted after centrifugation at 3000 revolution/min for 15 minutes at 4 °C. The levels of iron, ferritin, transferrin, transferrin receptor 1, total iron binding capacity, and hemoglobin will be measured using enzyme-linked immunosorbent assay.

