#### High-Resolution Magnetically SWI

All participants will undergo SWI, and the data will be postprocessed and analyzed using Susceptibility Mapping and Phase Artifacts Removal Toolbox software (The Math Works Inc) to obtain QSM images. Signal processing in Nuclear Magnetic Resonance software (Philips Healthcare Netherlands Ltd) will then be used to detect and quantitate the corrected phase value in the region of interest, including bilateral parietal cortex, frontal white matter, caudate nucleus, putamen, globus pallidus, thalamus, red nucleus, substantia nigra, hippocampus, and dentate nucleus [21,22,28]. Care will be taken to avoid blood vessels, calcifications, and visible lesions during the measurements. Each site will be measured twice, and the average of the 2 measurements will be taken. The magnitude of magnetization will be used to indicate the level of iron content of the tissue.

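### No outcome is named primary and one P<.05 rule covers at least 19 outcomes and 48 correlations, so chance findings are likely and neither primary objective is tested at a known error rate

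*Protocol article*

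**What the plan says.** Research Objectives gives two primary objectives: clinical efficacy, and whether acupuncture acts through brain iron deposition and body iron metabolism. Neither is tied to a named outcome.

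The Overview under Outcome Measurements ranks nothing: "The 3 main areas of assessment will include neuropsychological tests, SWI, and serum iron metabolism". The measures under it are:

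- three scales: MMSE, MoCA and Clinical Dementia Rating (CDR);
- six serum indicators: "The levels of iron, ferritin, transferrin, transferrin receptor 1, total iron binding capacity, and hemoglobin";
- ten brain regions: "bilateral parietal cortex, frontal white matter, caudate nucleus, putamen, globus pallidus, thalamus, red nucleus, substantia nigra, hippocampus, and dentate nucleus".

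MoCA appears in Sample Size as the outcome behind the calculation ("We set the significance level at .05"), but no section calls it primary.

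Statistical Analysis treats scales, serum indicators and brain iron alike as measurement data and states: "All statistical results will be considered statistically significant at" P<.05. Normal data get one-way ANOVA followed by least significant difference (LSD) comparisons. Non-normal data get Kruskal-Wallis followed by Mann-Whitney tests with Bonferroni correction. Scale scores are then correlated with the serum and brain iron measures in the patients by Pearson correlation. No adjustment across outcomes, regions, correlations or visits is stated.

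**The concern.** A significance rule controls error only for the set of tests it was designed for. Here one threshold is applied to every test, and nothing says which test decides either objective. MoCA drove the sample size calculation but has no special place in the analysis. If MoCA misses, the text does not stop another scale from carrying the efficacy conclusion. For the mechanism objective, any of 16 or more iron measures, or any of dozens of correlations, could be presented as significant.

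The stake is interpretability. When the trial reports, a reader could not tell a finding that the plan set out to test from one that crossed .05 among many, and could attach no error rate to either conclusion.

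**Working it through.** **Reproducing the plan's own figure.** Inputs from Sample Size: "When α=.05 and β=.1, checking the table shows that" the normal quantiles are 1.96 and 1.282; "larger SD and mean difference between the 2 groups with values of 5.38 and 3.47, respectively"; and "considering a 20% shedding rate".

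- N = 2 × [(1.96 + 1.282) × 5.38 / 3.47]² = 50.53, rounded up to 51 per group.
- 51 / (1 − 0.20) = 63.75, rounded up to 64 per group. This matches the stated 64, so the calculation is for one two-sided MoCA test at .05 with 90% power.

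**Counting the tests.**

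- Outcomes: 3 + 6 + 10 = 19; with sides separate, 3 + 6 + 20 = 29.
- Correlations: 3 × (6 + 10) = 48; with sides separate, 3 × (6 + 20) = 78. This is per run. The protocol does not say at which visit, or on raw or change scores, they are run.

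**Chance of at least one false positive** with no true effects and independent tests, 1 − 0.95^k, and the expected number, 0.05k:

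| Family | k | Chance of at least one | Expected number |
|---|---|---|---|
| Three scales | 3 | 14.3% | 0.15 |
| All outcomes, sides pooled | 19 | 62.3% | 0.95 |
| All outcomes, sides separate | 29 | 77.4% | 1.45 |
| Correlations, sides pooled | 48 | 91.5% | 2.4 |
| Correlations, sides separate | 78 | 98.2% | 3.9 |

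**Allowing for correlated measures.** The documents give no correlations, so these values are assumed. Correlation changes the chance of at least one false positive but not the expected number.

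- The same correlation between all outcomes: at 0.5, about 13% for 3 tests, 41% for 19 and 50% for 29; at 0.7, about 11%, 28% and 33%.
- Correlation only within each block (scales 0.5 to 0.8, serum and brain 0.3 to 0.7), simulated with 2 × 21 patients: 40% to 69% for outcomes and 55% to 93% for correlations.

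**Allowing for the stated Bonferroni step.** Over three group pairs, the acupuncture-control contrast is tested at .05 / 3 = .0167. If every outcome took that route, independence would give 1 − (1 − .0167)^19 = 27% and 1 − (1 − .0167)^29 = 39%. The step does not touch the correlations.

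**Power if MoCA is the single primary test**, Φ(3.47 / (5.38 × √(2/n)) − 1.96):

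- n = 21 per arm: Φ(2.090 − 1.96) = 55%.
- n = 17 per arm (21 × 0.8 = 16.8, rounded): Φ(1.880 − 1.96) = 47%.

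**The case against.** **The roles are partly separated.** The Abstract's Methods judge efficacy on neuropsychological scores and use the correlations to explore mechanism. On that reading the efficacy family is three scales, with a false positive chance of 11% to 14% over assumed correlations of 0.7 down to 0, and an iron result cannot support an efficacy claim. This stands as a limit on size. It does not remove the point, because Research Objectives lists mechanism as primary and the Outcome Measurements overview ranks nothing.

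**A statistical plan may deal with multiplicity.** Data Collection and Management refers to one, and rules for secondary and exploratory families are often kept there. Their absence from an article is not the fault raised here. The fault is that the article fixes a blanket rule for all results, which a plan with multiplicity control would contradict, and names no primary outcome.

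**The pairwise procedures give some protection.** LSD after a significant ANOVA holds error near 5% within one outcome for three groups, and the Bonferroni route is stricter. CDR has only five possible values, so at least one scale may well take that route. Both act within one outcome only. The Abstract also has only the two patient groups reassessed after treatment, so a three-pair correction may not apply to the efficacy contrast at all.

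**Stronger readings the text does not support.** A reader might infer that false positives are near certain. That fits only the correlations, or everything pooled, with independent tests and no true effects. It does not fit the three scales or the outcomes as a whole. A reader might also infer that the protocol lets any one significant test satisfy an objective. It states no such success rule; it leaves the matter open.

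**Conclusion.** The point holds in this form: no outcome is primary, and a blanket P<.05 applies to at least 19 outcomes and at least 48 correlations, with correction only between group pairs within one outcome. Chance findings are therefore likely. With no true effects, about 1 to 1.5 are expected among outcomes (without the pairwise correction) and 2.4 to 3.9 among each run of correlations. Neither primary objective is tested at a known error rate.

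The percentages rest on all nulls being true. The highest also rest on independence, and the upper end of each range on analysing sides separately; the protocol supports neither assumption. The counts of 19 and 48 follow directly from the text. This should be corrected, but it does not invalidate the design.

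**What to change.** Before data lock, and while the analysts are still blinded, amend the protocol to:

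1. Name the week-4 MoCA comparison of acupuncture with control as the single primary efficacy test at two-sided .05, with MMSE and CDR secondary. The primary efficacy claim then has a 5% error rate.
2. Replace the blanket P<.05 sentence with a rule for each family. For blood markers, regions and correlations, either control multiplicity within the family (Benjamini-Hochberg at 5% is one option) or report estimates as exploratory without claims of significance.
3. State whether left and right are pooled, and at which visit and on which scores the correlations are run. Pooling and the exact families are design choices, not corrections of an error; they only need to be fixed in advance.
4. State the MoCA power at the planned size: about 55% at 21 per arm, or about 47% after 20% dropout, on the protocol's own difference and SD.

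Cost: no new patients, visits or measurements. It is, however, a documented protocol amendment made after about 30 enrolments, not a mere wording change. Fewer iron results will be nominally significant. The mechanism objective, now listed as primary, becomes exploratory, and the sponsor should accept that openly. Spreading .05 by Bonferroni over all outcomes instead would need .05/19 = .0026 or .05/29 = .0017, leaving MoCA power at about 18% or 15% with 21 per arm, so a single primary test is the more workable choice.

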**Methods:**

In total, 42 patients with VCI and 21 healthy individuals will participate in this clinical trial. The 42 patients with VCI will be randomized into acupuncture and control groups, while the 21 healthy individuals will be in the healthy control group. Both the control and acupuncture groups will receive conventional medical treatment and cognitive rehabilitation training. In addition, the acupuncture group will receive electroacupuncture treatment with Tongdu Xingshen for 30 minutes each time, 6 times a week for 4 weeks. Meanwhile, the healthy control group will not receive any intervention. All 3 groups will undergo baseline assessments of brain iron deposition, serum iron metabolism, and neuropsychological tests after enrollment. The acupuncture and control groups will be evaluated again at the end of 4 weeks of treatment, as described earlier. By comparing neuropsychological test scores between groups, we will examine the efficacy of Tongdu Xingshen acupuncture in treating VCI. Additionally, we will test the correlations between neuropsychological test scores, brain iron deposition, and body iron metabolism indexes to explore the possible mechanisms of Tongdu Xingshen acupuncture in treating VCI.

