#### Healthy Control Group

The healthy control group will receive no intervention.

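### The stated between-group test needs three groups, but only the two randomised arms are measured at week 4, so the efficacy comparison does not fit the design

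*Protocol article*

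**What the plan says.** The Statistical Analysis section treats scale scores, iron indicators and brain iron alike. The parametric route is "Normally distributed data with uniform variance among 3 groups will be analyzed using 1-way ANOVA", "followed by multiple comparisons using the least significant difference test". On the other route, "those with nonnormal distributions will be compared using the Kruskal-Wallis test followed by the Mann-Whitney" test, with Bonferroni correction. No two-group, change-score or baseline-adjusted test is named.

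The abstract makes this the efficacy test: "By comparing neuropsychological test scores between groups, we will examine the efficacy of Tongdu Xingshen acupuncture in treating VCI". It also fixes who is measured when. First, "All 3 groups will undergo baseline assessments of brain iron deposition, serum iron metabolism, and neuropsychological tests after enrollment". Then, "The acupuncture and control groups will be evaluated again at the end of 4 weeks of treatment".

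The Randomization section randomises only the 42 patients, 1:1. The healthy participants stand outside that: "The healthy control group will receive no intervention". The Sample Size section uses a two-group formula for MoCA at alpha .05.

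The Trial Design and Setting section and Table 1 list baseline and post-treatment assessments without saying which groups the later ones cover. Nothing in the article schedules a second cognitive, serum or imaging assessment for healthy participants.

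**The concern.** The efficacy question concerns two randomised arms at week 4. The only procedure named takes three groups, and the third has no week-4 data. Someone following the text must either drop the healthy group, which the text does not say, or carry its week-0 values forward into a week-4 comparison.

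If the values are carried forward, people outside the randomised comparison affect how it is tested, in three ways:

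- LSD divides the acupuncture-control difference by an error term pooled over all three groups.
- The omnibus test that precedes LSD responds to the gap between patients and healthy people, so it gives little protection to the treatment comparison.
- On the Kruskal-Wallis route, correcting for three pairs lowers the level for the one pair that matters.

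The distributional checks that choose the route also take in the healthy group, and one outcome of those checks, normal data with unequal variances, leads to no test. At stake are the level and the power of the trial's efficacy test.

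**Working it through.** **The plan's own figure.** Inputs from the Sample Size section: SD 5.38, difference 3.47, Z values 1.96 and 1.282, 20% loss.

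N = 2 × [(1.96 + 1.282) × 5.38 / 3.47]² = 50.53, rounded up to 51; 51 / 0.8 = 63.75, rounded up to 64 per group. The stated 64 reproduces. It is a two-group calculation at two-sided .05, with no third group and no correction for three pairs.

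**Inputs for the check.** From the article: 21 per group, patient SD 5.38, control mean 22.66, difference 3.47. Assumed, because the article gives neither: healthy mean 28, and healthy SD from 2 to 7. Data are simulated as normal, and healthy values are taken to be reused at week 4.

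**Error term.** With equal group sizes the pooled SD is √[(2 × 5.38² + s²) / 3], where s is the healthy SD. At s = 3 this is √[(57.89 + 9) / 3] = 4.72, or 0.88 of the patient SD. The LSD test uses 60 degrees of freedom instead of 40.

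**Omnibus gate and LSD with no treatment effect:**

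| Healthy SD | Pooled SD / patient SD | Omnibus F significant | LSD type I error, trials passing the variance check |
|---|---|---|---|
| 2 | 0.84 | 99% | branch almost never reached |
| 3 | 0.88 | 98% | about 8% to 9% |
| 4 | 0.92 | 97% | about 7% |
| 5.38 | 1.00 | 91% | about 5% |
| 7 | 1.11 | 81% | about 3% |

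The variance check is Levene's test at .05. It is passed in about 2% of trials at SD 2, about 38% at SD 3 and most trials at SD 4 or above. A two-sample t test on the two arms alone stays at about 5% throughout.

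**Kruskal-Wallis route.** Three pairs give .05 / 3 = .0167. For a true difference of 3.47 with 21 per arm:

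| Test | Power |
|---|---|
| Mann-Whitney at .0167 | about 32% |
| Mann-Whitney at .05 | about 51% |
| t test at .05 | 53% |

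The 32% barely depends on the healthy SD, because the loss comes from the correction.

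**Missing branch.** ANOVA requires normality and equal variances, while Kruskal-Wallis is reserved for nonnormal data. Normal data with unequal variances fall between the two. With a healthy SD of 2 and patient SD of 5.38, simulated normal data fail Levene's test in roughly 96% to 98% of trials, so this gap is easily reached.

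**The case against.** The strongest reply is that the harmful reading is nowhere stated. No sentence says that week-0 healthy values will be reused, and a three-group comparison is proper at baseline, where all three groups are measured. If only the randomised arms enter at week 4, one-way ANOVA is the two-sample t test, and the pooled-error and omnibus problems vanish, as does the three-pair correction. The Data Collection and Management section refers to a statistical plan that is not shown and may contain a two-arm test. This stands as far as it goes: a reader might infer that the trial has no two-arm test at all, and the article cannot show that. But the article does set out a specific procedure for its efficacy comparison, and that procedure does not match its own visit schedule or sample-size basis.

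Three further inferences are tempting and should not be drawn.

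- *Type I error is 8.5% to 11%.* Those figures apply LSD to every simulated trial with a healthy SD of 1.5 to 3. The plan admits only data with uniform variance. At SD 2 about 2% of trials pass. Error among those few is about 13%, but that amounts to about 0.3% of all trials. With equal SDs there is no inflation, and with a larger healthy SD the test is conservative.
- *The low-power branch would be the usual one.* Failing the variance check does not lead to Kruskal-Wallis; only nonnormality does. In normal-data runs at least one group failed a Shapiro-Wilk test in only about 14% to 15% of trials. MoCA ceiling effects could raise that, but this was not quantified.
- *The healthy comparison is faulty for lack of matching or age and sex adjustment.* An article commonly leaves these details to the full protocol or analysis plan, so their absence is not an error here.

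Two limits on the figures also stand. The power figures come from normal data, although that branch is meant for nonnormal data. The ceiling argument concerns cognitive scales; no distortion has been shown for serum iron or susceptibility values.

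**Conclusion.** The point holds as a mismatch between the stated test and the design. The only between-group procedure in the article cannot be run with three groups at week 4 on the data the article says will be collected, unless baseline healthy values are reused. This conclusion needs no assumption about the healthy group.

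The size of the harm is conditional on that reuse. The direction and amount of the LSD error depend on a healthy SD that the article does not give: modest inflation at SD 3 to 4, none at equal SDs, and conservatism above that. The firmer cost is the three-pair correction, which takes about 19 percentage points of power (51% − 32%) from the efficacy comparison wherever that route is followed. The roughly 53% power available to a two-arm t test at 21 per arm is a consequence of the sample size and is separate from this point.

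**What to change.** Rewrite the between-group paragraph of the Statistical Analysis section in two parts.

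1. **Efficacy.** Compare acupuncture with control at week 4 by one prespecified two-arm analysis at two-sided .05 that does not require equal variances. A Welch t test or a linear model with robust standard errors would serve. Use no healthy data, no omnibus gate and no Bonferroni correction over three pairs. No distributional pretest is then needed to choose the test, and the missing branch disappears.
2. **Healthy group.** Restrict the three-group, or patients-versus-healthy, comparison to baseline, and label it observational.

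If a statistical plan already contains such a two-arm test, bring the article's description into line with it. The cost is one paragraph and no new data or visits. The change should be made and dated before the locked database goes to the statisticians.

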### Inclusion and Exclusion Criteria

#### Inclusion Criteria

Inclusion criteria are as follows: (1) aged 18-75 years, male or female; (2) patient or informant reports of memory loss or other cognitive impairment lasting for at least 3 months and not using any medication to improve cognitive function prior to enrollment; (3) diagnostic criteria for VCI are met (Western medical diagnostic criteria refer to the *2019 Chinese Guidelines for the Diagnosis and Treatment of Vascular Cognitive Disorder* and Chinese medical diagnostic criteria refer to the *Diagnostic, Identification and Efficacy Determination Criteria for Vascular Dementia*); (4) imaging evidence (computed tomography or magnetic resonance imaging) to support cerebrovascular disease; (5) clear cognitive dysfunction, as assessed by the MMSE (no education: MMSE score≤17, primary school: MMSE score≤20, or junior school or above: MMSE score≤24) and MoCA (MoCA score < 26 points); and (6) consciousness and stable vital signs.

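### Each outcome's test is picked from the observed distribution, normal data with unequal variances have no test, and the multiplicity correction changes with the branch, so the branch can decide significance

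*Protocol article*

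**What the plan says.** The Statistical Analysis section of the protocol article puts all outcomes under one rule: "Neuropsychological scale scores, iron metabolism–related indicators, and brain iron deposition are all measurement data". It then gives two branches.

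- Normal with equal variance: "Normally distributed data with uniform variance among 3 groups will be analyzed using 1-way ANOVA", then LSD pairwise tests, which are not adjusted for multiplicity.
- Nonnormal: "those with nonnormal distributions will be compared using the Kruskal-Wallis test followed by the Mann-Whitney" U test, here with a Bonferroni correction.

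The choice of summary statistics splits the same way. Mean and SD are used "If the data involved satisfy the characteristic properties of a normal distribution with uniform variance"; otherwise, "if the data are not normally distributed, we will use the median and IQR to describe them". The threshold is common to all outcomes: "All statistical results will be considered statistically significant at" P<.05. The section names no check of normality or variance and assigns no outcome a test beforehand. It gives no method for normal data with unequal variances and no separate test for the two randomized arms.

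**The concern.** The rule has three weaknesses.

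1. **It depends on the data.** With 21 per group, checks of normality and variance are noisy, so an outcome can change branch by chance. Its estimand then moves between means and ranks.
2. **It is incomplete.** Normal data with unequal variances have neither a test nor a summary. The design makes unequal variances plausible. Patients must have "MoCA (MoCA score < 26 points" on a 30-point scale whose normal range starts at 26, so healthy controls with normal scores have only 26 to 30 to spread over.
3. **The branches differ in stringency.** LSD tests each pair at .05, whereas Bonferroni over three pairs tests at .05/3. A shape check therefore sets the significance level for acupuncture versus control.

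At stake is whether a result is declared significant because of the treatment or because of the branch. Where variances differ, the analyst must also choose a method after seeing the data.

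**Working it through.** **Inputs.** Sample Size section: week-4 MoCA 26.13 (SD 5.33) versus 22.66 (SD 5.38), difference 3.47, and "When α=.05 and β=.1". Trial Design and Setting: 21 per group. Assumed, because the article does not give them: Shapiro-Wilk in each group and Levene across groups, each at .05; for the simulations, a patient mean of 20 before any treatment difference, a healthy mean of 27, and a healthy SD varied from 5.38 down to 2.

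**The plan's own figure.** N = 2[(1.96 + 1.282) × 5.38/3.47]² = 50.53, so 51 per arm; 51/0.8 = 63.75, so 64. This reproduces.

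**Leaving the ANOVA branch by chance.** For truly normal, equal-variance data, three Shapiro-Wilk tests and one Levene test all pass with probability of about 0.95⁴ = 0.81. Simulation (4,000 runs) agrees: ANOVA 81%, Kruskal-Wallis 14%, no test 5%. So about 19% leave the ANOVA branch.

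**What the branch does.** Acupuncture versus control, equal SDs, 21 per arm (6,000 runs):

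| Procedure | Type I error | Power at 3.47 |
|---|---|---|
| LSD after significant ANOVA | 5.1% | 53% |
| Mann-Whitney at .05/3 after Kruskal-Wallis | 1.7% | 31-32% |

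At the planning effect the two procedures disagree on significance in about 22-23% of simulated trials.

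**Where the difference comes from.** At the same alpha of .05, the t-test has about 54% power and Mann-Whitney about 51-52%. At .05/3 they have about 35% and 32%. So only 2-3 of the roughly 21 points come from means versus ranks. The rest comes from correcting one branch and not the other.

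**How often no test applies (three groups).**

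| Healthy SD (assumed) | Normal scores | Rounded, capped at 0-30 |
|---|---|---|
| 5.38 | 5% | 2% |
| 4 | 18% | 14% |
| 3 | 52-54% | 38% |
| 2 | 84% | 68% |

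**If pooled ANOVA/LSD is run anyway.** With healthy SD 3, the pooled variance is about (5.33² + 5.38² + 3²)/3 = 22.1, against (5.33² + 5.38²)/2 = 28.7 in the patient arms. The standard error is too small by a factor of √(22.1/28.7) = 0.88. With healthy SD 2 the pooled variance is (5.33² + 5.38² + 2²)/3 = 20.5 and the factor is √(20.5/28.7) = 0.85. Simulated type I error for acupuncture versus control is 8.6% and 9.2% respectively (8.5-9.6% across repeated simulations). Welch's test stays at about 4.5-5.5%.

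**The case against.** The strongest reply is that the efficacy comparison is largely untouched. The Abstract's Methods have only the two patient groups evaluated again after 4 weeks, and their planning SDs are nearly equal (5.33 and 5.38). In a two-arm comparison the gap occurs in about 5% of trials, which is simply Levene's nominal error, and there is one contrast and no Bonferroni penalty. Choosing the test by pre-testing, with Welch filling the gap, then gives 4.7% type I error and 54% power, the same as a fixed t-test. This stands, with one limit: the Statistical Analysis section gives no two-arm test, so following it literally makes acupuncture versus control a post hoc contrast of a three-group analysis.

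Four stronger readings that a reader might infer are not supported:

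- That ranks in place of means cost some 20 points of power. The loss is almost all Bonferroni.
- That Levene's rejection rate is the frequency of the gap (60% at healthy SD 3, 98% at SD 2). The gap also needs normality, and scores compressed under a ceiling often go to Kruskal-Wallis, which the plan does cover.
- That a definite number of the trial's outcomes will switch branch by chance. The 19% assumes truly normal data, while the Clinical Dementia Rating (CDR) has five levels and MMSE and MoCA are bounded integers.
- That MoCA must move to a rank method. The Sample Size section plans it on a mean difference.

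It can also be said that assumption checks and fallbacks belong in a separate statistical plan, which Data Collection and Management mentions. That would answer silence. Here the article states the selection rule itself, and the rule as stated is incomplete and uneven.

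**Conclusion.** The point holds as a defect in a stated rule. The selection depends on the data, omits one case, and ties the multiplicity correction to the branch, so the branch can decide significance. Under the assumed checks, about 19% of truly normal, equal-variance three-group comparisons leave ANOVA by chance. The branches then have about 53% and 32% power at the planning effect, mainly through the unequal correction.

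The unequal-variance gap belongs chiefly to the baseline comparison with healthy controls. Its size rests on a healthy SD that the article does not give: roughly 38-54% of trials at SD 3, 68-84% at SD 2, and 5% or less if the SDs are equal. It reaches the efficacy comparison only if healthy controls enter that analysis, in which case pooled LSD would have about 9-10% type I error at those SDs. The documents do not show that the week-4 two-arm result is otherwise compromised.

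**What to change.** Delete the data-dependent rule and fix one method per outcome before the data are analysed:

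- **Acupuncture versus control at week 4:** a two-arm comparison that does not assume equal variances (Welch, or a linear model with robust standard errors), with MoCA kept on a mean difference as in the Sample Size section.
- **Three-group baseline comparison:** Welch ANOVA with an unequal-variance post hoc test.
- **CDR:** an ordinal or rank method, since it has five levels.
- **Multiplicity:** the same rule whatever the method.
- **Sensitivity only:** the rank or mean alternative for each outcome.
- **Description:** mean, SD, median and IQR for every outcome.

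The cost is one paragraph and a few extra analyses. The efficiency loss when variances are truly equal is very small: simulated power is 52.5% for Welch against 53.0% for LSD.
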